## Abstract

**Supplementary Information:**

The online version contains supplementary material available at 10.1186/s12877-026-07071-z.

## Background

Geriatric depression is a worldwide public issue and is becoming more prevalent with population aging. Nearly 12.95% to 28.4% of people older than 60 years experience depression [1, 2], of whom 7.3% meet DSM-IV criteria of major depression (MDD), although only 0.5% are considered to receive adequate treatment [3]. Minimally adequate treatment (MAT) for major depression ranges from 23.0% in high-income countries to 3.0% in low- and lower middle-income countries [4]. This inadequate treatment coverage for geriatric depression remains a major barrier to older adults’ mental health and well-being.

Modifiable lifestyle factors, particularly physical activity and sleep quality, play a crucial role in maintaining physiological and psychological functions in older adults [5–7]. For instance, physical activity and sleep quality revealed significant main effects and significant interaction effect on cognitive function among older adults [8]. From the lifestyle psychiatry perspective, research has established that both the onset and symptoms of various mental disorders (i.e., depression) are also linked to modifiable lifestyle factors, such as physical activity and sleep [9]. Empirical research has demonstrated that behavioral interventions targeting sleep disturbances [10, 11] and physical activity/exercise exert benefits on depressive symptoms [12]. For adults with non-severe depression, exercise has shown no difference in effectiveness compared with pharmacological interventions [13]. Interventions aiming at promoting sleep, such as practices related to sleep hygiene, have demonstrated a positive impact on alleviating depression [14, 15]. In addition, exercise has also been shown to improve sleep quality in older adults [16], indicating that it may have synergistic positive effects with sleep on depression. Besides these, our previous study demonstrated an economic benefit from combined physical activity and sleep intervention for older adults with depression. Specifically, we employed a target trail emulation approach controlling both base and time-varying covariates and found that for older adults with depression, adopting regular exercise and adequate sleep could significantly reduce long-term healthcare expenditures and the risk of catastrophic healthcare expenditure. Practice guidelines for mood disorders indicate that actions involving lifestyle changes are foundational and essentially non-negotiable to all patients [17]. Additionally, in most regions, people with mental issues often experience psychological distress and are stigmatized [18], highlighting the importance of implementing interventions carrying potentially destigmatizing effects.

Muscle-brain crosstalk has emerged as a pivotal mechanism for explaining the antidepressant effects of exercise, particularly in the context of geriatric depression where somatic comorbidities like sarcopenia are prevalent [19, 20]. Central to this dialogue is the exercise-induced myokine irisin, which is cleaved from FNDC5, acts as a hormone on several distant targets, including the brain. That is, its ability to cross the blood-brain barrier positions it as a key mediator of exercise’s effects on the central nervous system [8, 21], which can likewise contribute to increased brain-derived neurotrophic factor levels. Critically, exercise-induced skeletal muscle contraction increases blood concentrations of peripheral factors, such as the brain-derived neurotrophic factor (BDNF) and irisin, which have been shown to improve sleep depth in animals [21, 22]. Furthermore, sleep homeostasis is often associated with stress-related mental disorders, including depression [23]. It is reasonable to infer that sleep improvement might directly or indirectly alleviate depression by regulating the BDNF levels. Additionally, while serum is the most commonly used sample for detecting irisin and BDNF, previous study suggested that both saliva and serum sample would represent a valid and less invasive method for irisin detection [24]. Saliva BDNF has also been established as a valid biomarker in mental health research [25, 26]. Therefore, quantifying these biomarkers in saliva is expected to provide crucial insights into the pathophysiological mechanisms underlying geriatric depression and the therapeutic potential of our integrated exercise-sleep intervention.

The major limitations of existing trials are as follows. First, previous studies have predominantly employed single-component interventions (exercise or sleep health promotion) rather than developing multi-component intervention packages, despite evidence showing that the integrated interventions combining physical activity and sleep health are effective and acceptable for older adults [7, 15]. Furthermore, socio-ecological factors have to be proved to influence the success of lifestyle interventions [27]. For instance, promoting sustainable exercise among older adults requires attention to contextual factors such as social support, accessible infrastructure, security, and social position. Therefore, a comprehensive intervention package should consider both the integration of core health behaviors and its cost-effectiveness. Second, the majority of studies rely heavily on subjective measures, making it difficult to elucidate the potential pathways of intervention effects More objective outcomes, such as those derived from accelerometry, electroencephalogram (EEG), and salivary biomarkers, should be incorporated to complement the outcome assessment framework. These multi-faceted measurements are collectively designed to elucidate both the effects of the intervention and their underlying mechanisms. Third, previous trials have generally included participants with above threshold-level depression (i.e., MDD) and have rarely focused exclusively on subthreshold depression. However, even subclinical depressive symptoms in older adults are associated with reduced quality of life and functional impairment [28, 29], underscoring the need for greater attention to this population.

Randomized controlled trials (RCTs) are considered as the most robust research design for establishing a cause-effect relationship between interventions and outcomes. Such studies have typically been conducted to evaluate the effectiveness of exercise or sleep interventions among community-dwelling older adults in prior studies [11, 14, 15, 30]. However, parallel RCTs may be impractical or unethical in certain circumstances. Furthermore, because the intervention group receives the intervention simultaneously, it cannot analyze the impact of intervention timing (i.e., intervening late versus intervening early) on outcomes. The stepped-wedge cluster-randomized trial (SW-CRT) is a variant of the cluster trial design which allows all clusters to sequentially undergo the intervention and act as their own controls during the study period [31, 32]. Thus, this design can determine whether the timing of the intervention impacts its effectiveness by exploring the effect of intervention sequence. The SW-CRT also ensures that more participating clusters are exposed to the intervention at the end of the study, thereby enabling researchers to control time effects and consequently improve the precision of the study. This is also a preferable design on ethical grounds because it deploys the transformation at all communities for stakeholders, rather than having some of them serve solely as controls” [33]. Furthermore, a SW-CRT design is particularly recommended for testing an intervention with strong evidence to yield beneficial effects or that is very unlikely to cause harm (i.e., exercise and sleep intervention for older adults) [32, 34], as is the case in our study. Another notable strength is that the SW-CRT design is the only feasible alternative, given that logistical, practical, or financial constraints prevent simultaneous intervention delivery to all participants. When it comes to specific areas, especially the study of sub-clinical or mild-to-moderate mental problems, the SW-CRT design offers distinct advantages. In older adults, depressive symptoms are known to fluctuate over time and be affected by seasons, weather, major life events, etc. These symptoms also show a natural tendency to remit spontaneously [35]. In such time trends are subsumed into the error term or are unbalanced across groups, they could confound the effect estimate. The core strength of the SW-CRT is that its sequential rollout of the intervention across multiple time points enables the modeling and statistical control of such underlying time trends, separating them from the true intervention effect.

To address these gaps, the Geriatric Exercise-Sleep Optimization (GESO) trial protocol was designed by adopting a SW-CRT design. The primary aim is to evaluate the clinical efficacy of an integrated exercise-sleep intervention for alleviating depressive symptoms among community-dwelling older adults, with a particular interest in those with subthreshold depression. Secondary aims are to explore potential underlying mechanisms of the intervention by assessing salivary biomarkers (BDNF and irisin) and EEG; and to evaluate the cost-effectiveness of the intervention from a public healthcare system perspective.

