### Randomization and blinding

Initially, all six communities will begin in the control phase. Subsequently, two communities will be randomly allocated to the 12-week intervention period, followed by two other communities 12 weeks later, and the final two communities 12 weeks after that. Trial randomization will be performed by an independent researcher not otherwise involved in the study. Each community will be notified of its own transition date after recruiting first participant but will not be notified of the transition dates of other communities. Details of the randomization schedule are given in Fig. 1.

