### Sample size

Power calculation was performed using the PASS software module ‘Tests for Two Means in a Stepped Wedge Cluster Randomized Design’. Key input parameters were derived from a similar previous study [47], which reported a mean reduction in depressive symptom of 4.0 in intervention group compared to 2.0 in control group among community-dwelling older adults with depression. Based on our stepped-wedge design with 6 clusters, 2 clusters crossing over per sequence, an intra-cluster correlation (ICC) of 0.1, a planned sample size of 22 per community, a desired power of 90%, a two-side α level of 0.05, and an estimated 20% dropout rate, a total sample size of 165 participants will be required.

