### Statistical analyses

Analyses will include descriptive summaries and preliminary unadjusted comparisons between phases (control vs. intervention) and clusters. Specifically, variables within each phase or clusters will be described using descriptive statistics (means and 95% confidence intervals for normal distributed quantitative variables; medians and interquartile ranges for non-normally distributed quantitative variables).

Analyses of data from a SW-CRT requires specific methodological considerations to account for its design, including the control of secular trends (period effects) and the assessment of potential carryover effects. Guided by methodological recommendations for SW-CRTs [60], we will choose Method 3 to evaluate the intervention effects of the integrated exercise-sleep intervention. This method treats the intervention variable as a time-dependent categorical variable, comparing groups with different numbers of intervention measurements with all the control measurements. This allows us to examine whether the effect of the integrated exercise–sleep intervention varies with the length of exposure, thereby informing the time dependency of treatment effects, including potential carryover.

All models will be estimated using multilevel mixed-effects regression to account for the hierarchical structure of the data. We will first fit a two-level (time and individual levels) and a three-level (time, individual, and community levels) mixed-effects model without any potential confounders. Then, we will further adjust the selected model (based on model fit criteria) by including study period (time) as a fixed effect. Third, an adjustment will be made for the baseline value of the outcome variable and associated baseline covariates (e.g., socio-demographics, cognition), and in the fourth step, both an adjustment for the follow-up time, the baseline value of the outcome variable, and related covariates will be performed. To evaluate the time dependency of the effect of starting the intervention, an interaction term between intervention and time can be added to the model [60, 61]. Additionally, we will account for potential between-cluster variations by including relevant community-level covariates (e.g., socio-cultural characteristics and access to health services) as fixed effects in the models, if they show preliminary associations with the outcome.

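### The Background claims the design can settle early versus late intervention, but the last pair of communities starts with no concurrent control, so any late-start effect depends on an assumed effect shape

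*Protocol article*

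**What the plan says.** The Background argues that a parallel trial cannot examine "the impact of intervention timing (i.e., intervening late versus intervening early) on outcomes". It then states that "this design can determine whether the timing of the intervention impacts its effectiveness by exploring the effect of intervention sequence".

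Randomization and blinding gives the rollout: "Initially, all six communities will begin in the control phase". Two communities then start, "followed by two other communities 12 weeks later, and the final two communities 12 weeks after that". Sample size confirms a "stepped-wedge design with 6 clusters, 2 clusters crossing over per sequence".

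Statistical analyses enters study period as a fixed effect. It chooses a method that lets the effect differ by number of intervention measurements. To study dependence on starting time it adds that "an interaction term between intervention and time can be added to the model". The coding of time in that interaction is not given.

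Table 1 lists outcomes at baseline, 6 weeks and 12 weeks only. Late versus early start is not among the aims at the end of the Background.

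**The concern.** A stepped wedge separates the intervention effect from calendar time by comparing communities that have started with communities still waiting. When the third pair starts, nobody is waiting. The late end of the early-versus-late comparison therefore lacks the feature that the Background relies on.

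Calendar time matters here by the protocol's own account. The Background names season, weather and life events as influences on symptoms, and says that "These symptoms also show a natural tendency to remit spontaneously". An early-versus-late result reported from this trial could reflect the last calendar period, or the form chosen for the model, and still be presented as a randomised finding about timing. The Background sentence invites that reading.

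**Working it through.** **Inputs.** Six communities, two per step, three steps 12 weeks apart after a common control phase (Randomization and blinding); ICC 0.1, 22 per community, planned difference 4.0 - 2.0 = 2.0 points, 20% dropout (Sample size). Fig. 1 is not shown, so one initial control period followed by three 12-week periods is assumed.

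**The plan's own figure.** 6 x 22 = 132, and 132 / 0.8 = 165. This reproduces the stated total and does not depend on the timing question.

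**Communities by period.**

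| Period | Started | Still in control |
|---|---|---|
| 1 | 0 | 6 |
| 2 | 2 | 4 |
| 3 | 4 | 2 |
| 4 | 6 | 0 |

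**Why the last effect is aliased.** Write the mean in period t as b(t) for control and b(t) + d(t) for intervention. Periods 2 and 3 contain both kinds of community, so d(2) and d(3) can be estimated. In period 4 every community has mean b(4) + d(4), and only the sum is observed.

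**Rank of the fixed-effect design matrix, categorical periods.**

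| Intervention effect modelled as | Earlier communities still measured | Measurement stops 12 weeks after own start |
|---|---|---|
| one effect per period | 6 of 7 | 6 of 7 |
| one constant effect per sequence | 7 of 7 | 6 of 7 |
| common exposure profile plus sequence shift | 9 of 9 | late shift not estimable |
| free sequence-by-exposure effects | 9 of 10 | 6 of 7 |
| one effect plus a linear interaction with time | 6 of 6 | 6 of 6 |

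Wherever the rank falls short, the third-sequence effect is what is lost. First versus second start is estimable in every row.

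**What the full-rank models assume.**
- *Linear interaction:* d(4) is not observed but set to d(3) + [d(3) - d(2)]. If d(2) = -2.0 and d(3) = -1.5, the model returns d(4) = -1.0 whatever happens in period 4.
- *Constant effect per sequence:* the earlier communities supply b(4), on the assumption that their effect has not changed since their 12-week course. Suppose the true effect is the same in all sequences: -2 in the first 12 weeks, then -1, then 0. Generalised least squares with ICC 0.1 and 22 per community per period then gives -1.57, -2.48 and -3.43 for sequences 1 to 3. The late-minus-early difference is -1.87 (from unrounded values), although the true difference is 0. An effect growing from -2 to -3 to -4 gives +1.87.

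**Precision of the comparison that has concurrent controls.** Take 22 per community per period, ICC 0.1, within-person correlation 0 to 0.7 and community autocorrelation 0.8 to 1 (the last two assumed), without readings after each community's own 12 weeks. The standard error of second minus first start is 0.19 to 0.39 SD. On the same data the overall effect has 0.095 to 0.20 SD, so the ratio is about 2.0. If later readings are included, the contrast between the period-2 and period-3 effects has about 1.7 times the standard error of the overall effect.

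The protocol gives no SD. The SD at which 22 per community per period gives 90% power for 2.0 points is about 4.05. At that SD, 0.19 to 0.39 SD is 0.77 to 1.58 points, and a 95% interval is about ±1.5 to ±3.1 points (1.96 x 0.77 and 1.96 x 1.58).

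**The case against.** The strongest reply is that the trial does carry some information on timing. The first two pairs are randomised to earlier or later start, and each has concurrent controls (two started against four waiting, then two newly started against two waiting). This stands, and it is why the timing analysis should be narrowed and kept.

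A second reply is that the third-sequence effect can be estimated under some models. This also stands. A reader might infer that the late effect can never be separated from calendar time, or that software must drop the term. The documents do not support that: the coding of the interaction is not stated, one linear term is full rank, and constant sequence effects are estimable if earlier communities are still measured in the last period. Table 1 points to measurement ending at 12 weeks, whereas the exposure-length method and its interest in carryover point the other way, and Fig. 1 is not shown. But each of these routes replaces the missing controls with an assumed shape, and constancy is the assumption that Statistical analyses declines to make when it lets the effect vary with length of exposure.

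A reader might also infer that late starters will have remitted while waiting, so that a smaller late effect must be a floor effect. The entry threshold is PHQ-9 of at least 5 and no re-check at crossover is stated, so this is possible. It is not shown, because the article does not say when participants are recruited relative to their community's step.

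Finally, the sentence is Background rationale, the interaction is optional, and the limitations paragraph already concedes time contamination and analytic complexity. That limits the weight of the point, but the limitations do not mention timing and the unqualified claim remains.

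**Conclusion.** The point holds in a limited form. The rollout leaves no control community when the last pair starts. Early minus late (sequence 1 against sequence 3) is therefore not estimable when intervention effects are free to differ by categorical period, and otherwise rests on an assumed effect shape. A wrong shape can create a spurious timing difference of 1.87 points, nearly the whole planned effect. The one comparison with concurrent controls, first against second start, has about twice the standard error of the overall effect and sets two communities against two.

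The aliasing needs only the stated rollout and categorical periods. The standard errors also rest on the assumed four-period layout, 22 per community per period and the correlation ranges shown. A reader should not infer that the main intervention effect is compromised: timing is not a stated aim, and the primary estimate, power and sample size do not depend on it.

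**What to change.** 1. **Background.** Replace the statement that the design can determine the impact of timing with one saying that it allows a limited, exploratory comparison of the first two start times.
2. **Statistical analyses.** Restrict the intervention-by-time analysis to the two steps that have concurrent control communities. Report it as exploratory, with a confidence interval, next to the mean PHQ-9 at the start of intervention in each sequence, so that differences in room to improve can be seen.
3. **Statistical analyses.** State that any effect given for the third sequence is model-dependent, and name the assumption used.

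The cost is wording and a narrower optional analysis. The sponsor gives up a secondary claim that the design does not support. Conduct, recruitment and the primary analysis do not change.

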## Methods

### Design and settings

The GESO project is a pragmatic, open-labeled, stepped-wedge cluster randomized trial incorporating qualitative process and economic evaluations. A concise causal model diagram was showed in Supplementary 1. This study will be conducted in accordance with the SPIRIT (Standard Protocol Items: Recommendations for Interventional Trials) statement [36].

This study will be conducted in six communities in Urumqi City, Xinjiang Uygur Autonomous Region, China. Participating communities will be selected based on diverse geographic distribution, participant sociodemographic characteristics, and approval from local administrative committees. We will distribute flyers containing relevant information about our study to older residents, and invite them to attend their local community centers for assessment and the consent process.

### Participants and recruitment

Participants meeting the following criteria will be included: (1) aged 60 years or above; (2) current depressive symptoms as measured by the Patient Health Questionnaire-9 (PHQ-9) score ≥ 5. The exclusion criteria are: (1) cognitive impairment indicated by a score < 26 on the Montreal Cognitive Assessment (MoCA); (2) contraindications to exercise (e.g., uncontrolled hypertension or diabetes mellitus, unstable angina); (3) current participation in any other intervention program. All participants will provide written informed consent.

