### Study procedure

All eligible participants will run over a 12-week integrated exercise and sleep intervention. A trained GESO research assistant will contact potential participants via face-to-face meeting, telephone call, or online platforms (e.g., voice call or video call) to introduce the study, discuss participation, answer questions, and determine eligibility. Then, eligible participants who express willingness to join will then provide a signed written informed consent. For participants contacted remotely (via telephone or online) will sign the informed consent form during the baseline assessment.

To minimize participant burden, we will deliberately distribute all assessments across the study period. Specifically, subjective measurements (i.e., questionnaires and scales) will be collected at the beginning of the first week. Then, researchers will equip with the ActiGraph accelerator device (GT3X) and give usage instructions for each participant. After a one-week monitoring period, participants will be required to return the device. The saliva sample and resting-state EEG will be collected within one week after allocation and post-intervention (12-week) according to participant availability. Notably, the EEG and saliva collection are part of an optional sub-study on mechanisms. For those who consent to this sub-study, we offer flexible scheduling and transportation assistance to facilitate participation. Participation is voluntary and does not affect involvement in the main trial or compensation. Other proactive strategies in order to enhance engagement and minimize dropout include a dedicate research assistant to maintain weekly contact, offering a highly flexible schedule, providing small, tiered compensation after each major time point, and giving personalized guidance and feedback on participants’ health conditions and improvements.

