### Interventions

Based on the literature review [37–39] and our previous study, a preliminary integrated intervention framework was developed for older adults with depression. The intervention consists of two core components: a multi-component exercise and sleep hygiene education (SHE). These components are theoretically and practically synergistic and are delivered in a coordinated manner over the 12-week period, supported by behavioral activation (BA) techniques to facilitate adherence and behavior change [40, 41].

Exercise component: The exercise program is primarily based on the Otago Exercise Program [42] and will be refined in consultation with sports experts. It is designed as three time-stratified regimens to align with circadian rhythms and daily routines:Morning regimen (10 minutes): Focusing on low-intensity activation and circadian entrainment upon waking, involving dynamic stretching and light exposure.Afternoon regimen (20 min): Constituting the core exercise session, including low to moderate intensity aerobic exercise, resistance training, and balance training. Exercise intensity will be standardized using the Borg Rating of Perceived Exertion (RPE 6–20) scale. Participants will be trained to maintain an RPE between 11 and 16 (low to moderate intensity) during the aerobic session [43, 44].Pre-sleep regimen (15 min): Aiming at promoting physiological and cognitive relaxation within 1 h of bedtime, primarily consists of flexibility training. Participants will also be encouraged to incorporate brief ‘zero-time’ activities throughout the day to interrupt sedentary behavior or physical inactivity.Sleep component: The SHE is based on established sleep hygiene recommendations [45]. It comprises structured behavioral advice concerning modifiable lifestyle and environmental factors associated with sleep quality [11]. Key education topics include regulating sleep-wake schedules, optimizing the bedroom environment (e.g., reducing light and noise), scheduling napping, managing caffeine and alcohol intake, and establishing a pre-sleep wind-down routine.

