The two components are integrated into a unified, home-based intervention package. BA techniques including goal setting, activity scheduling and monitoring, reinforcement, and relaxation training, will be incorporated into the 12-week intervention implementation to support the adoption and maintenance of the integrated exercise-sleep intervention. In the control phase, participants will be advised to maintain their normal daily activities and will only receive minimum contact (once per week) to reduce the pre-intervention attrition. The final integrated intervention will be refined through a preliminary test with 20 participants based on rationale about feasibility. Detailed description of the intervention, according to the template for intervention description and replication (TIDieR) checklist [46], is provided in Supplementary 2.

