EEG is a non-invasive, economical method to explore the electrocortical brain activity, and also has been applied to capture functional activity in interventional studies [57, 58]. Resting-state EEG data will be collected at baseline (T0) and post-intervention (T2) for exploring the neurophysiological mechanisms of the intervention. To facilitate participation and minimize burden, we will offer all participants flexible scheduling, transportation assistance or reimbursement to the lab, and a guided, relaxed assessment experience in a dedicated facility. EEG measurements will take place in a dimly lit room within the School of Psychology at Xinjiang Normal University. Participants will sit in a relaxed position, with their backs supported by the chair and both hands comfortably resting on a table in front of them. They will be instructed to perform an average of 12 min (10 to 15 min) eye-closed resting-state task followed by a 3-minute eyes-open resting condition. Data will be acquired using an ANT amplifier (Compumedics Neuroscan, SynAmps2,) equipped with a 64-channel active electrode cap arranged according to the international 10–20 system. Three electrooculogram (EOG) channels will be used to detect ocular artifacts. All signals will be referenced online to Cz and grounded at AFz, and digitized at a sampling frequency of 500 Hz. Electrode impedances will be maintained below 10 kΩ. Data will be processed and analysed with MATLAB R2024a (MathWorks, Natick, MA) in conjunction with the EEGLAB toolbox (v.2025.0.0) and custom-written scripts. All signals will be filtered using a 1 Hz high-pass filter, 80 Hz low-pass filter, and 50 Hz notch filter, then be down-sampled to 500 Hz.

Based on previous exploratory neurophysiological studies in older populations, we anticipated a good participation rate in this assessment. The resulting sample size for EEG analysis is expected to be sufficient for generating preliminary hypotheses regarding intervention-related neurophysiological changes, consistent with similar exploratory mechanistic studies. Study enrolment and assessment procedures are described in Table 1.

**Table 1 Tab1:** Schedule of enrolment and assessments

Timepoint	-T1	T0	T1	T2
	Enrolment and allocation	Baseline	6-week	12-week
Enrolment				
Eligibility screen	×			
Informed consent	×			
Allocation	×			
Assessment				
Demographic information		×		
Primary outcomes				
Depressive symptom: PHQ-9		×	×	×
Depression remission rate		×	×	×
Secondary outcomes				

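### Table 1 places the check for exercise contraindications at enrolment only, so in this stepped wedge it need not be current when home exercise starts

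*Protocol article*

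**What the plan says.** - **Criterion.** Participants and recruitment, exclusion (2), lists "contraindications to exercise (e.g., uncontrolled hypertension or diabetes mellitus, unstable angina"). It gives no time at which this is judged.
- **When it is judged.** Under Study procedure, a research assistant contacts potential participants, in person or remotely, "to introduce the study, discuss participation, answer questions, and determine eligibility". Consent follows. Table 1 has one row for this, "Eligibility screen", with one mark, under enrolment and allocation (-T1). There is no mark at baseline, 6 weeks or 12 weeks.
- **When exercise starts.** Randomization and blinding states: "Initially, all six communities will begin in the control phase". Two communities then cross over, "followed by two other communities 12 weeks later, and the final two communities 12 weeks after that".
- **What happens in between.** Under Interventions, control-phase participants "will only receive minimum contact (once per week) to reduce the pre-intervention attrition".
- **What the exposure is.** A home-based programme whose core afternoon session combines aerobic, resistance and balance work. For the aerobic part, "Participants will be trained to maintain an RPE between 11 and 16 (low to moderate intensity) during the aerobic session".

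**The concern.** The other two screening measures, PHQ-9 and MoCA, define who is studied, and one measurement at entry serves that purpose. Criterion (2) is different. It guards against an exposure, and its examples are conditions that are uncontrolled or unstable at the time of assessment. In a parallel trial with immediate start, a screen at enrolment is close to the exposure. A stepped wedge separates the two by design, and the separation grows with the step.

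The schedule as written lets a participant pass the screen, wait in the control phase, come to meet criterion (2) while waiting, and begin home exercise without breaking any rule in the article. At stake is mainly whether a safety exclusion does its job at the moment it is needed. It also matters that the criterion is applied on the same footing in all three sequences, because the Background section wants to read differences between sequences as an effect of intervention timing.

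**Working it through.** **Inputs.** From Sample size: 6 clusters, 2 per sequence, 22 per community, 20% dropout, total 165. From Randomization and blinding: steps of 12 weeks and an initial control phase for all. The length of that initial phase is not in the text, and Fig. 1 is not shown.

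**1. The plan's own total.** 6 × 22 = 132, and 132 / (1 − 0.20) = 165. This reproduces the stated figure. With equal communities, each pair holds 165 / 3 = 55 participants.

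**2. Share that starts after the first pair.** 4 / 6 = 66.7%. That is 165 × 4/6 = 110 enrolled participants, or 132 × 4/6 = 88 after the planned dropout.

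**3. Lag behind the first pair.** Exactly 12 weeks for the second pair (about 55 participants) and exactly 24 weeks for the third (about 55).

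**4. Wait from screen to exercise.** This is the interval that matters, and the article does not give it. Suppose everyone enrols at trial start and the first control period lasts c weeks (assumption). The wait is then c, c + 12 and c + 24 weeks.

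| c (assumed) | First pair | Second pair | Third pair | Share waiting at least 12 weeks |
|---|---|---|---|---|
| 0 | 0 | 12 | 24 | 2/3 |
| 6 | 6 | 18 | 30 | 2/3 |
| 12 | 12 | 24 | 36 | all |

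A participant who enrols r weeks after trial start waits r weeks less, so rolling recruitment within communities would shorten these intervals. The text fixes only one point about recruitment timing: "Each community will be notified of its own transition date after recruiting first participant". That places the start of recruitment before the community learns its date, but does not say how long before.

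**5. Does anything else in the article do the job of a later check?**
- The weekly control-phase contact has retention as its only stated purpose.
- Study procedure also mentions personalised feedback on health, but lists it among measures to keep participants engaged and does not link it to criterion (2).
- The Discussion contrasts the home-based format with group training under an instructor, so no on-site session is described at which a changed condition would be noticed.
- Table 1 covers one 12-week cycle (baseline, 6 weeks, 12 weeks). It cannot show where the screen falls relative to the control phase or the crossover, because it has no column for either.

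**The case against.** The strongest reply is that this is an article, and pre-exercise procedures commonly sit in the full protocol or the intervention description. Supplementary 2 is cited for the latter and is not shown. Nothing in the article says that contraindications are not checked again. This stands, and it limits the claim. A reader might infer that the exclusion is definitely not applied when exercise begins; the documents do not establish that. What they do establish is that the one schedule shown puts the check at enrolment and leaves its relation to the start of exercise undefined.

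A second reply is that Table 1, read at face value, runs from enrolment straight into a 12-week intervention cycle, so the screen would fall just before exercise. That reading does not fit the Interventions section, which has enrolled participants in a control phase with measures against attrition before the intervention. The two accounts need reconciling.

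A third reply concerns contrasts between sequences. A reader might infer that the first pair is freshly screened and only the later two thirds are affected. The text does not support this: the first pair also begins in control, and with a 12-week initial period every participant would wait at least 12 weeks. A reader might also take 12 and 24 weeks as minimum waits from screening. They are lags behind the first pair, not waits from screening. Finally, a count of participants who would start exercise while meeting the exclusion needs an incidence that the documents do not give, so none is offered.

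**Conclusion.** The point holds in limited form. Table 1 ties the assessment of criterion (2) to enrolment, while the crossover schedule and the control-phase description separate enrolment from exercise. As written, the criterion need not be current when exercise starts. Four of six communities, about 110 of 165 participants assuming equal community size, start 12 or 24 weeks after the first pair. The actual interval per participant is unknown. It ranges in the table above from 0 to 36 weeks under enrolment at trial start and an assumed initial period of 0 to 12 weeks, and would be shorter with rolling recruitment.

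It may be tempting to go on to a bias in the timing effect, through fitness for exercise that differs by sequence. The documents do not show such a difference or give a means of sizing it. The case for change rests on the safety exclusion and on applying it uniformly. It is more than a missing detail, because the schedule places the check at a point that the design separates from the exposure. Confidence is moderate, since a later check may exist in material not shown.

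**What to change.** Reconcile Participants and recruitment, Randomization and blinding, the control-phase text under Interventions, and Table 1. The schedule should show when the existing criterion (2) is assessed relative to each community's start of exercise, in the same way for all three sequences. This needs Table 1 to include the control phase and the crossover. If a later check already exists elsewhere, a mark in the table settles the matter.

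State also that anyone found to meet the criterion at that point stays in follow-up and is analysed under the community's scheduled phase, in line with the intention-to-treat principle in Statistical analyses. The PHQ-9 and MoCA criteria need not be applied again. The timing of the check and the clinical management of those concerned are for the investigators.

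The cost is one short check at a contact that already takes place and an amended table. The statistical price is a slight dilution of the intention-to-treat effect if a few participants do not receive the exercise component. The sample size does not change.
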